**Figure 6 figure6:**

Patient timeline in this randomized controlled trial.

### Feasibility Study

To access the feasibility of the RCT (eg, whether patients after surgery can handle the devices), we conducted a small-scale trial with 8 patients in 2018. These patients followed the procedure for the intervention group in the RCT, except that the trial duration was only 1 week. Feasibility was assessed based on the usage data of the devices and the mobile app, a questionnaire that measures relevant psychological variables, and an interview (face-to-face or by phone call).

### Statistical Analysis

For the outcome variables of interest, that is, average daily steps, overall compliance rate, and physical fitness measured in the bicycle ergometer test (peak VO_2_, maximal workload, HR_max_), the following 2-step procedure will be used. In the first step, independent sample *t* tests (unpaired) will be used to compare the outcome variables between the two study conditions. Second, when potential confounding variables are identified post hoc, they will be added to multiple regression models to control for their influences. For step data at the day level, multilevel models will be built to test the same hypotheses, with patient ID as the grouping variable [55]. We will use the conventional α level of .05 to judge for statistical significance, and more importantly to use the estimated effect sizes in order to judge the clinical significance of the effects.

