## Methods

### Design

The study (registered at Netherlands Trial Register NL8040) will have a parallel-group randomized experimental design with an allocation ratio of 1:1. Participants will be randomized to the intervention or the control group during the introduction meeting at the date of discharge (Figure 1). Variables regarding participants’ psychological states (eg, self-efficacy toward PA) will be measured repeatedly over the weeks during the experiment (see the “Outcomes” section for details). The protocol conforms to the SPIRIT 2013 statement [30] and is described according to the CONSORT-EHEALTH checklist [31] (Multimedia Appendix 1).

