### Sample Size Calculation

We used a minimum effect size of interest approach to calculate the sample size needed to detect a statistically significant difference between the intervention group and the control group in terms of the primary outcome (average daily steps over 3 weeks). In an internal discussion between researchers, physicians, and CR experts at CZE, a 2000-step daily difference was proposed to be the minimum effect size of interest, and a 3000-step within-group standard deviation was assumed based on [32]. These assumptions amount to a moderate to strong effect size in terms of Cohen *d* of 0.67, which is justifiable given the large differences between the two conditions in terms of costs. Based on a simulation study in the R statistical programming environment [33], 100 participants (50 in each group) are required to have a 90% power to detect the effect at a significance level of .05. Because we will also have day-level data for steps over 3 weeks, multilevel regression models can also be used for examining the differences in PA between the two groups, which should have much higher power due to the large number of observations (ie, data collected over 21 days by 100 patients). Details of the simulation-based power analysis (and the R code) can be found in Multimedia Appendix 2.

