### Primary and Secondary Outcomes

The primary outcome is the amount of daily physical activities by the patients, operationalized as the average daily steps over the 3 weeks. The steps are measured by the Axivity AX3 tracker, which is a CE-marked 3-axis logging accelerometer developed by the Open Movement organization at Newcastle University (Figure 5). The device is intended to be used in research on activity recognition, motion measurement, medical research, and movement science. It has been used previously in a large-scale clinical trial in UK [39] and validated for measuring PA in older adults [40]. Patients in both intervention and control group will be asked to wear the device as a clip on their cloths at their hip on the nondominant side (eg, a belt clip). The device has a long battery life (around 1 month) and large internal memory (1-month’s data with a sampling frequency of 50 Hz), so the patients do not have to worry about charging the device or offloading the data. Unlike the self-tracking device (the Neo Health One), this measurement device only records data but provides no feedback about steps to the patients.

In addition to the primary outcome, 2 secondary outcomes are used to test whether the behavioral-level increase of daily PA levels would bring patients benefits at physical and psychological levels for their preparations for the formal CR program. To measure physical fitness, a bicycle ergometer test will be held for each patient at the Cardiac Function Department as their usual clinical practice within 1 week after the 3-week trial. The research team will not be involved in the administration of the test, but 3 parameters of interest, namely, peak oxygen uptake (peak VO_2_), maximal workload, and maximum heart rate (HR_max_), will be provided to us. Previous studies have shown positive effects of walking trainings on physical fitness [41-43]. However, because of the short duration and moderate intensity of our exercise program, we do not strongly predict significant effects given the sample size.

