### Additional Measurements for Exploratory Analyses

Besides primary and secondary outcomes and demographic and clinical data collected as part of the usual care, we will also collect app usage data and additional self-report measures for exploratory analyses. App usage data can provide preliminary insights into the role of specific features of the app in its overall effectiveness by correlating outcome variables with usage metrics, including login frequency, frequency of monitoring one’s step data (Figure 4C), coaching message frequency, and coaching message content.

Additional self-report measures are used to assess patients’ baseline PA levels before their cardiac events and to examine the dynamics of their psychological states over the weeks between the intervention and the control group. A complete list of the self-report measures in English can be found in Multimedia Appendix 2. All questions will be translated into Dutch for the trial.

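### The fitness outcomes are compared by unadjusted t tests, with covariates added only if identified as confounders after the fact; a covariate set fixed in advance would be more precise and leave no data-driven choice of model.

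*Protocol article*

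**What the plan says.** Primary and Secondary Outcomes and Patient Timeline place the ergometer test within 1 week after the 3-week programme. Neither section describes a test before it. The three parameters passed to the researchers are peak VO2, maximal workload and HRmax.

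Statistical Analysis sets a two-step procedure for these parameters, together with average steps and compliance. Step 1: "In the first step, independent sample *t* tests (unpaired) will be used to compare the outcome variables between the two study conditions". Step 2 adds variables to multiple regression models, but only where they have been recognised post hoc as possible confounders. No covariate is named. On the threshold: "We will use the conventional α level of .05 to judge for statistical significance". The same section says that estimated effect sizes matter more than significance.

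Additional Measurements for Exploratory Analyses refers to "demographic and clinical data collected as part of the usual care", and a questionnaire score of physical activity before the cardiac event is also collected.

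On what to expect for fitness, the protocol says: "because of the short duration and moderate intensity of our exercise program, we do not strongly predict significant effects given the sample size".

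**The concern.** Exercise capacity differs between adults before any treatment effect, for example with age, sex and body size. With no pre-programme ergometer value described, all of that variation stays in the error term of an unadjusted comparison.

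Step 2 does not reliably remove it. A search for confounders looks for variables on which the arms differ. A strong predictor that chance has balanced is not a confounder in that sense and would not enter, yet it is the kind of variable that reduces residual variance. Because the search is post hoc, the covariates are also chosen once the data are available, and the section does not say which estimate prevails if steps 1 and 2 disagree.

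Better fitness is part of the justification for the technology in the abstract's Objective and part of the main hypothesis in the Discussion. The Discussion also says that an unconfirmed hypothesis may imply that the programme without technology is sufficient. An imprecise null on fitness would therefore be interpreted, and avoidable width in its confidence interval matters.

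**Working it through.** **The plan's own figure.** Sample Size Calculation concerns steps only: "a 2000-step daily difference was proposed to be the minimum effect size of interest" and "a 3000-step within-group standard deviation was assumed", so d = 2000/3000 = 0.667. It concludes that "100 participants (50 in each group) are required to have a 90% power to detect the effect at a significance level of .05". Sidedness is not stated. With n = 50 per arm and two-sided .05, the noncentrality is d × √(n/2) = 0.667 × 5 = 3.33 on 98 df, and power is 91.0%. The exact t calculation needs 49 per arm. The stated 100 therefore reproduces as a two-sided calculation; a one-sided .05 would need only 39 per arm by the normal approximation. That d belongs to steps and is not used below.

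**Inputs for fitness.**
- From the documents: 50 per arm, 1:1 allocation, alpha .05.
- Assumed: two-sided test; an ergometer result for all 100 patients; standardised effect d from 0.2 to 0.5; R2 of 0.10 or 0.25, with 0.50 as an optimistic case; three covariates.

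**Formulas.**
- Residual SD after adjustment = SD × √(1 − R2).
- Noncentrality = d × √(50/2) / √(1 − R2) = 5d / √(1 − R2), on 98 df unadjusted and 98 − 3 = 95 df adjusted.
- 95% CI half-width in SD units = t(.975, df) × √[(2/50) × (1 − R2)].
- Equivalent unadjusted sample size = 100 / (1 − R2).

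**Worked case, d = 0.4, R2 = 0.25.** Unadjusted noncentrality is 5 × 0.4 = 2.00, power 50.8%. Adjusted noncentrality is 2.00/√0.75 = 2.31, power 62.8%.

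**Power by noncentral t:**

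| d | Unadjusted | R2 = 0.10 | R2 = 0.25 | R2 = 0.50 |
|---|---|---|---|---|
| 0.2 | 16.8% | 18.1% | 20.8% | 28.8% |
| 0.3 | 31.8% | 34.7% | 40.3% | 55.6% |
| 0.4 | 50.8% | 55.1% | 62.8% | 79.9% |
| 0.5 | 69.7% | 74.2% | 81.5% | 93.8% |

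**CI half-width.**
- Unadjusted: 1.984 × √0.04 = 0.397 SD.
- R2 = 0.10: 1.985 × √0.036 = 0.377 SD.
- R2 = 0.25: 1.985 × √0.03 = 0.344 SD.

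**Equivalent sample size.** At R2 = 0.25, 100/0.75 = 133 patients; at R2 = 0.10, 100/0.90 = 111.

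**Cost of the degrees of freedom.** If the covariates explained nothing (R2 = 0), moving from 98 to 95 df would change the half-width by less than 0.001 SD.

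**The case against.** The strongest reply is that nothing here is wrong. In a "parallel-group randomized experimental design with an allocation ratio of 1:1" the unpaired t test is valid and unbiased without a baseline value. Step 2 does allow adjustment, and covariates for a secondary outcome are often left to the analysis plan, which is not shown. The gain rests entirely on assumed values. If the fitness effect is as small as the protocol seems to expect, power stays low either way: 16.8% against 20.8% at d = 0.2 with R2 = 0.25.

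Much of that stands. The loss is one of efficiency, and its size cannot be taken from the article. The appeal to an unseen analysis plan carries less weight, because the article does not leave the matter open. It states a rule for when covariates enter, and Expected Results for the Main RCT says the analyses will follow the method reported in the protocol.

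Four stronger readings are tempting and not supported:
- A reader might infer that the protocol admits the fitness comparison is underpowered. It does not use that word. It says it does not strongly predict significant effects given the sample size, and gives the programme's short duration and moderate intensity as the reason.
- A reader might infer that no adjustment is planned. Step 2 plans it, but conditionally and post hoc.
- A reader might apply the 90% power and d of 0.67 to fitness. Both are for steps.
- A reader might take age, sex and weight as named covariates in hand. The article says only demographic and clinical data; age and sex are a fair inference, and weight is less certain.

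**Conclusion.** The point holds as a loss of precision and an open modelling choice, not as bias or a calculation error. The confounder rule leaves out balanced prognostic covariates and lets the adjusted model depend on the data.

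If the covariates explain a quarter of the variance, the gain is 4 to 12 percentage points of power for d between 0.2 and 0.5, and an interval about 13% narrower (0.344/0.397 = 0.87). At R2 = 0.10 the gain is 1.3 to 4.5 points. These figures assume two-sided testing, complete ergometer data and the stated R2 values. The case for fixing the covariates in advance does not depend on R2. The change is worth making, but the trial's validity does not turn on it.

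**What to change.** In Statistical Analysis, replace the post hoc confounder step for the fitness outcomes with a linear regression of each parameter on study condition plus a small covariate set named in advance and included whether or not the arms look imbalanced. Age and sex are the obvious candidates. Body weight could be added if it is in the usual-care record and suits the unit of peak VO2, which the article does not state. The pre-event activity score is a further option. Its timing should be checked first, because the first questionnaire is sent after discharge and so after allocation.

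Report the adjusted mean difference with its 95% CI as the main fitness result and the unadjusted t test as support. Settle this before outcome data are seen.

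The cost is a sentence or two of text and about three of 98 degrees of freedom, with no new visits, tests or patients. If the covariates predict little, little is gained and almost nothing is lost. The change does not supply the missing pre-programme ergometer value; it only recovers some of the precision that such a value would have given.

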#### Physical Activity Levels Before Cardiac Events

Patients’ regular PA levels before their cardiac events will be measured using the validated International Physical Activity Questionnaire [46], available in Dutch.

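### Daily steps are tested three ways at .05 with no analysis named as decisive, and the adjustment covariates are to be chosen post hoc

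*Protocol article*

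**What the plan says.** The primary outcome is physical activity, "operationalized as the average daily steps over the 3 weeks" (Primary and Secondary Outcomes), so each patient contributes one value. The Statistical Analysis section sets out two steps for the outcome variables: unpaired t tests between groups, and then adjustment: "when potential confounding variables are identified post hoc, they will be added to multiple regression models to control for their influences". It adds a third analysis of the same question: "For step data at the day level, multilevel models will be built to test the same hypotheses, with patient ID as the grouping variable". A single level of .05 applies throughout. No analysis is called primary, no candidate covariates are listed, and no selection rule is given.

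The Sample Size Calculation section sizes the trial on the three-week average. It then offers multilevel models as a further option and expects them to have much higher power.

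Baseline activity is collected: "regular PA levels before their cardiac events will be measured using the validated International Physical Activity Questionnaire". It appears among the measures for exploratory analyses and is not named as a covariate for the primary outcome.

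**The concern.** Three analyses of one hypothesis can give three p values on different sides of .05, and the text does not say which would be the trial's answer. The article presents the multilevel model as the more powerful option, so it reads as a rival test and not as a sensitivity check.

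Post hoc covariate choice makes this worse. In a "parallel-group randomized experimental design with an allocation ratio of 1:1" baseline imbalance arises by chance, so adding covariates because they look imbalanced, or because they change the result, is not needed for validity and opens a route to a preferred p value. The wording also does not limit the choice to variables fixed before randomisation. Attitude and habit strength are measured weekly after allocation, and app usage is also post-allocation. Adjusting for such variables could remove part of the effect under test.

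This is more than detail left to an analysis plan. The article itself commits to post hoc selection, and its section on expected results says the analyses will follow the method reported in the protocol.

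**Working it through.** **1. Reproduce the sample size, to see which analysis it belongs to.** Inputs from Sample Size Calculation: "a 2000-step daily difference was proposed to be the minimum effect size of interest", a standard deviation of 3000 steps, and "100 participants (50 in each group) are required to have a 90% power to detect the effect at a significance level of .05". Sidedness and dropout are not stated; two-sided and no dropout are assumed.

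- d = 2000/3000 = 0.667.
- n per group = 2(z₀.₉₇₅ + z₀.₉₀)² × 3000²/2000² = 2 × (1.960 + 1.282)² × 2.25 = 47.3, so 48.
- By the noncentral t distribution, power is 89.8% at 48, 90.4% at 49 and 91.0% at 50 per group (noncentrality 0.667 × √25 = 3.33, 98 df).
- A one-sided test would need only 39 per group.

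The stated 100 therefore fits a two-sided, unadjusted t test on patient means.

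**2. Type I error under the plan as written.** Null trials were simulated with 50 per group, 5000 per scenario (Monte Carlo standard error near 5%: √(0.05 × 0.95/5000) = 0.3 points). The documents give none of the following, so all are assumptions:

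- Independent baseline covariates together explain the stated share (R²) of between-patient variance in steps.
- Day-level variance is 0.8 of between-patient variance.
- In three of the four scenarios, 30% of patients have only 3 to 20 usable days out of 21.
- The multilevel model is approximated by a regression of patient means weighted by days available.
- Imbalance rule: adjust for covariates differing between groups at p < .10.
- Free choice: smallest p among the unadjusted test, each single-covariate model, the all-covariate model and the multilevel model.

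| Candidates, R², patients with missing days | t test alone | Imbalance-adjusted regression alone | Multilevel alone | Any of the three, imbalance rule | Free choice |
|---|---|---|---|---|---|
| 5, 10%, 30% | 4.8% | 4.4% | 4.8% | 5.6% | 7.9% |
| 5, 25%, none | 4.9% | 3.9% | 4.9% | 5.6% | 10.0% |
| 5, 25%, 30% | 5.0% | 4.3% | 4.9% | 5.9% | 10.0% |
| 8, 40%, 30% | 4.8% | 3.4% | 4.9% | 6.0% | 11.4% |

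The t test holds its level. Almost all of the inflation comes from covariate choice; the multilevel model adds little. Regression adjusted only for imbalanced covariates is itself off nominal, on the conservative side.

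**3. Power if one covariate is fixed in advance.** Adjustment for a covariate correlated r with steps changes the effect size to d/√(1 − r²). The documents give no r. At 50 per group:

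- r = 0.2: 0.667/0.980 = 0.680, power 92.1%.
- r = 0.3: 0.667/0.954 = 0.699, power 93.3%.
- r = 0.5: 0.667/0.866 = 0.770, power 96.8%.

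Splitting alpha over three analyses instead (.05/3 = .0167) would cut the power of the t test to 81.3%.

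**4. When baseline activity is recorded.** Under Patient Timeline, allocation takes place in the discharge meeting and the first questionnaire is emailed right after discharge. Under Randomization and Blinding, patients know their group. The article does not say which questionnaire carries the activity measure, but the earliest one follows allocation. The measure concerns the pre-event period, yet the report is given by a patient who already knows the assignment.

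**The case against.** The best defence is that the t test is already primary in all but name. It comes first in an ordered procedure, the outcome is one average per patient, and the sample size reproduces as a t test on those averages. That stands as an implication, but the article never says it, and its remark on the higher power of multilevel models points the other way.

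Several stronger readings are tempting and are not supported:

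- **That the error rate of the headline result exceeds 5%.** This follows only if more than one analysis may count. The t test alone holds its level.
- **That inflation is 14% or 28%.** Three independent tests would give 1 − 0.95³ = 14.3%, but these analyses share the same data and are highly correlated. A figure near 28% appears only when the best p is taken over all subsets of five independent covariates, each correlated 0.4 with steps. That means R² = 5 × 0.16 = 0.80, which is implausible for daily steps. The plan says identified confounders will be added, not that the best subset will be sought.
- **That the baseline activity measure is wasted.** It has a stated exploratory use and could enter the second step. It is simply not prespecified for the primary analysis.
- **That post-randomisation variables will be adjusted for.** The article speaks of confounders and treats compliance, attitude and habit as outcomes. The fault is only that nothing excludes them.

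Missing late days could lower a patient's average, since prescribed walking rises weekly. A group bias would also need missingness to differ between groups, and its size would rest on assumed step counts. Feasibility wear was 54 of 56 days, though over one week only. That is a secondary matter and not part of this point.

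**Conclusion.** The point holds in a limited form. The protocol fixes three tests of the primary hypothesis at .05, names none as decisive, and commits to choosing covariates after the fact. The harm is conditional: none if the t test is held to be the answer, about 5.6–6.0% type I error if any of the three may count under an imbalance rule, and about 8–11% under free choice. These figures rest on assumed covariate strength (R² 10–40%), 5 to 8 candidates and the limited set of models searched; a wider search would give more. The flaw should be corrected before data are seen, because a choice of decisive analysis made afterwards would not be credible.

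**What to change.** Before any outcome data are seen:

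1. Name one confirmatory analysis of average daily steps, tested at two-sided .05. The existing t test would suffice. A regression or mixed model with a short, fixed list of pre-randomisation covariates, including pre-event activity, is preferable. Choose the rest of the list from the demographic and clinical data of usual care, which the article does not itemise.
2. Label the remaining analyses supportive. Label any post hoc adjustment exploratory and limit it to variables fixed before randomisation.
3. Record the pre-event activity questionnaire before allocation, for example when consent is signed before the operation.

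The total of 100 need not change: power at 50 per group is 91.0% with the t test and about 93–97% with a covariate correlated 0.3–0.5 with steps. The cost is a reworded paragraph, one questionnaire moved earlier, a few degrees of freedom and less analytic freedom.
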